## Abstract

**Background:**

Since the Ghanaian National Health Insurance Scheme (NHIS) was introduced in 2004, coverage rates have remained low, despite affordable premiums and payment exemptions for minor, senior, poor, and pregnant individuals. While 82% of the population have registered with the NHIS, many fail to complete the annual renewal and thus lose their coverage. A mobile renewal service introduced in 2018 simplified the previously cumbersome renewal procedure. Still, 40% of active member experience gaps in coverage in a given year, and 19% fail to renew at all. Baseline research suggests that forgetfulness is a major barrier to renewal.

**Methods:**

A total of 342,818 NHIS members from Kumasi will be randomized into the reminder, autorenewal or control groups. The reminder arm receives SMS prompts to complete the mobile renewal process and payment before expiration. The autorenewal arm is eligible to sign up for automatic renewal and give the NHIS permission to deduct the premium from their mobile money account, and will receive SMS prompt to do so. The intervention lasts 6 months. NHIS routine data will be used to evaluate the effect of the interventions on renewals. A follow-up survey household survey in Kumasi will evaluate additional aspects user experience.

**Discussion:**

Improving insurance retention has the potential to substantially increase health insurance coverage rates, as 45% of the Ghanaians currently have expired insurance. Assessing these tools will identify enabling factors and barriers of the intervention and inform the transferability of the intervention to other health insurance systems in sub-Saharan African countries.

**Trial registration: Pan African Clinical Trials Registry, PACTR202409918648487:**

Registered on 04 September 2024.

**Supplementary Information:**

The online version contains supplementary material available at 10.1186/s13063-025-09360-1.

## Introduction

### Background and rationale {6a}

Ghana implemented its National Health Insurance Scheme (NHIS) in 2004 in order to improve coverage and expand access to health care. While 82% of Ghanaians did register for NHIS membership at some point since the scheme’s inception, overall population coverage remains relatively low at about 52% of the population [1, 2]. Similar to health insurance schemes in other African countries, the NHIS relies on a system of annual re-enrolment of members [3]. This means that individuals have to actively renew their membership and, depending on their exemption status, may have to pay an annual premium and processing fee [2]. Members can renew their membership within 90 days before expiration. After the expiration date, there is a 90-day grace period in which the member can renew their membership without penalty and be able to instantly access care. After more than 90 days, the member can still renew but has a 30-day waiting period before insurance becomes active. This is done to discourage the likelihood of adverse selection of renewing health insurance only when needed. Children under 5, pregnant women, and elderly over 70 are exempt from this waiting period.

Mobile technologies are increasingly used to support national health financing systems and contribute towards improved population coverage [4]. In Ghana too, the National Health Insurance Authority (NHIA) introduced a mobile renewal service in 2018. Until then, the insurance renewal process required personal attendance at an NHIS Office, and a number of studies investigating the reasons and determinants of non-registration and non-renewal found that long queues and waiting times required for in-person registration were significant deterrents to renewal, along with other factors, including dissatisfaction with the quality of healthcare and financial constraints [5–9]. Now, the mobile renewal service enables members to complete their renewal easily via mobile phones, using mobile money for payment of processing fees and premiums. The system was quickly accepted, with ~ 70% of NHIS members renewing their insurance using the mobile renewal option [10], which has contributed to higher coverage rates among those who were previously less likely to be insured [2]. Despite this increase in convenience, around 50% of insurance periods are renewed either late or not at all each year. In a recent survey, members cited forgetfulness (19.8%), busy schedules (17.9%), and procrastination (15.6%) as reasons for non-renewal [11], which suggests that an intervention that reduces the logistical and organizational barriers may be effective in improving renewal rates.

Mobile phone-based reminders have been used in many countries and settings to improve adherence to medication or vaccination schedules, or to encourage timely preventative care or follow-up appointments [12–14]. Several studies have found text and voice message reminders to be effective in improving patient compliance and health outcomes [14–19]. However, to the best of our knowledge, reminders have not been used to remind people to renew their health insurance in African countries, except as part of a broader intervention [20].

Additionally, automatic renewal of health insurance may potentially contribute to higher coverage rates [21]. Automatic renewal converts health insurance renewal into the default option upon a one-time opt-in. It can be considered a form of nudging that exploits a default-bias, whereby individuals are more likely to comply with a goal if it is made the default option and requires no additional action [22]. In the USA, automatic renewal has been found to lead to increasing health insurance coverage by reducing administrative barriers [21]. However, again, to the best of our knowledge, automatic renewal has not been used in an African context.

Therefore, the ReachUHC project has co-conceptualized an intervention consisting of regular renewal reminders for the NHIS, combined with an automatic renewal option to address the problem of coverage gaps. This intervention is to be introduced in Kumasi, Ghana. The main research questions are threefold: (1) What are the effects of renewal reminders and the automatic renewal service on coverage gaps and renewal rates?; (2) which factors are supporting intervention implementation and uptake, and what is the role of contextual factors?; and (3) is the intervention relevant and transferrable to other sub-Saharan African countries, specifically Kenya, Nigeria, Rwanda, Tanzania, and Uganda?

### Objectives {7}

The hypothesis of the study is that the ReachUHC intervention consisting of mobile phone-based reminders and an opt-in autorenewal option for NHIS renewal will increase renewal rates and reduce coverage gaps in Kumasi, Ghana. The overall aims of the project are to assess effectiveness of the intervention, analyze implementation processes, and study relevance and transferability of the intervention:

Objective 1: Evaluate the effectiveness of the ReachUHC intervention at increasing renewal rates and reducing coverage gaps.Objective 2: Analyze user satisfaction, determinants of intervention uptake, and the need for intervention adjustment and improvement prior to national scale-up.Objective 3: Explore relevance and transferability of the intervention to five African countries: Kenya, Nigeria, Rwanda, Tanzania, and Uganda.

### Trial design {8}

This trial is a single-site RCT. NHIS members in Kumasi will be cluster-randomized by phone number into a parallel-group multi-arm superiority trial with a 1:1 allocation ratio to evaluate the effectiveness of renewal reminders and the autorenewal platform on active and recently expired members.

## Methods: participants, interventions, and outcomes

### Study setting {9}

Our study is conducted in the city of Kumasi, Ghana’s most populous city with 3.5 million inhabitants. We draw our study population from the 1.37 million NHIS members living in all of Kumasi’s Sub-Metropolitan Districts (Asawase, Asokwa, Bantama, Bosomtwe-Atwima-Kwanwoma, Manhyia, and Subin), and in one of its major suburban districts (Ejisu-Juaben). We chose Kumasi as our study site as it provides a diverse population in a populous, geographically contained area.

### *Eligibility criteria* {10}

Participants must have active or recently expired NHIS membership at the starting date of the intervention. If expired, the expiration date of their insurance must be no older than 1 October 2022.Participants must be identified as residents of the Kumasi districts either through the location in their member file in the NHIS database or through the survey or phone number verification exercise conducted in 2023.Participants must have a phone number which is registered as the primary phone number for no more than 6 NHIS members residing in Kumasi.

Often, the same phone number is used by mobile money vendors or community workers to manage the NHIS insurance membership for a larger group of community members who need help with mobile renewal or who do not have access to their own phone or phone number. Receiving reminders for more than 6 individuals may become a significant nuisance for the main phone number owner. In addition, such messages may be unlikely to reach intended recipients, as they are unlikely to reside in the same household. Therefore, we exclude phone numbers shared by more than 6 individuals.

During a phone number verification exercise conducted by the NHIA in September 2023, a group of 64,646 NHIS members in Kumasi was surveyed in order to verify or update their contact details and mobile phone number. All individuals who were surveyed as part of this exercise, the “verified number sample,” are recruited as participants. The individuals surveyed during the preliminary implementation research survey in February and March 2023 were also included in this verified sample (if they were NHIS members and fit the eligibility criteria). Furthermore, any individual identified as a Kumasi resident in the database who was not included in the verification exercise and fulfills the inclusion criteria is eligible to be randomly selected into the “unverified number sample,” which forms the remainder of the participants. The verified sample consists of a group of 61,097 eligible individuals, the unverified sample consists of 281,281 eligible members which were randomly drawn from all eligible Kumasi residents in the NHIS database.

### Who will take informed consent? {26a}

A waiver for informed consent has been granted from the Kwame Nkrumah University of Science and Technology Committee on Human Research, Publication and Ethics. We argue that informed consent is not needed in this case according to the requirements set forth by the Council for International Organizations of Medical Sciences (CIOMS), World Health Organization (WHO), and the US Department of Health and Human Services (HHS) that.Risk to participants is minimal [23]The research has important social value [23]The research could not be practicably carried out without the waiver [23, 24]The study is conducted by public health authorities and is designed to study a public service program, its procedures for obtaining benefits, and possible changes in those procedures [24]

Members will not be prospectively informed of their participation in the trial and will not be asked to consent to receiving SMS messages. However, the sign-up to the autorenewal platform is voluntary, and NHIS members who do not wish to receive further SMS communications from the NHIA can opt out any time via USSD menu. We consider this approach appropriate, as consent to receive SMS communications from the NHIA was given implicitly by all individuals who registered for membership with the NHIS. Since residents of Ghana commonly receive text message reminders for different subscriptions and memberships, an SMS reminder for health insurance renewal will not be unusually intrusive or present a significant burden. The sign-up for the autorenewal service is voluntary, and users may unsubscribe from it through a simple process in the USSD menu at any time. Furthermore, users are prompted to enter a PIN to authorize payment before funds can be deducted from their mobile money account, so consent for the payment will also be obtained. To the best of our knowledge, there is no conceivable risk or adverse effect which can be expected to result from these services. As we evaluate the participants using only anonymized routine data in the primary study, no further consent provisions will be required.

### Additional consent provisions for collection and use of participant data and biological specimens {26b}

For both the quantitative follow-up survey and the qualitative scale-up interviews, the administrators explain a prepared statement on informed consent (translated into applicable local languages) to all selected participants before administering the questionnaire and obtained a signature (or fingerprint) from the participant on the informed consent form. The statement of informed consent (1) provides a description of study goals and survey procedure; (2) asserts voluntary nature of participation and the right to withdraw anytime; (3) provides information over confidentiality, privacy, and intended use of survey data; and (4) assures that non-participation will not result in any disadvantages for the potential participant. After the statement has been explained, survey administrators offer to answer any questions that the potential participant may have. After all outstanding questions have been answered, the potential participant can choose to sign and date the form and enrol in the survey, or not sign the form and not enrol in the survey. The survey administrator also provides name, signature and date on the form as a witness to the consent given.

## Interventions

### Explanation for the choice of comparators {6b}

We break down our samples into 3 groups based on their membership status and expiration dates. Group 1 contains all individuals with active insurance and an expiration date during the intervention period. Group 2 contains all individuals with a currently expired membership and expiration date between 1 October 2022 and the end of the pre-intervention period. Group 3 contains all members with active insurance and an expiration date after the planned end date of our intervention period. We do this because expired members require different reminders and autorenewal messages than active members, and because those with a renewal date during the intervention phase receive messages around their expiration dates which individuals with renewal date outside of this time frame cannot receive. Furthermore, we expect that individuals with expired insurance may react differently than individuals with active insurance, and that those with more imminent renewal dates may respond differently than those whose renewal dates are still far away. We randomly allocate treatment within each group, clustering individuals by phone number to prevent spillovers. Group 3 is only assigned autorenewal or control, because the renewal window opens 90 days before expiration, therefore sending reminders to a group whose insurance expires in 6 months at the earliest would not be sensible.

Due to the randomization, the treatments and control within each expiration date group (1, 2, 3) arms only differ by the treatment status. Individuals in the control arms will not receive SMS prompts for renewal or autorenewal, but will otherwise receive usual communications from the NHIA which are not related to this trial. Only participants assigned to be treated in the autorenewal arm will be able to sign up for the autorenewal platform as primary users, but will be able to add other individuals (typically dependents and other family members) to their renewal plan and pay for their renewals. All other individuals will be able to access the USSD Menu of the autorenewal platform through the short-code, but will not be able to sign up for the service. Instead, they will be shown an error message informing them that this platform is still undergoing testing and may be made available at a later date (Fig. 1).

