#### Recruitment {15}

Recruitment for the intervention study consists of selecting members to target with SMS messages from the NHIS database and the verified number sample. The phone number verification exercise which was conducted in September 2023 will ensure that a high percentage of targeted individuals can be successfully contacted and thereby enrolled. The remaining participants are recruited and enrolled automatically from the NHIS database right before the start of the intervention, which ensures that a sufficient number of individuals will be successfully contacted, despite the limitations stemming from outdated or shared phone numbers.

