## Discussion

### Explanation of design choice

The phone numbers of members registered in the NHIS member database are often outdated. As a result, a renewal reminder sent to a number in the data base may not reach the intended recipient. Furthermore, an SMS message may reach an unintended recipient, because members sometimes register with a facilitators phone number (such as a local kiosk owner, NHIS staff, or medical staff), because phone numbers are passed on to friends or relatives, or because phone numbers are re-assigned by the telecommunications company after a period of inactivity. For a subset of 65,000 Kumasi residents, a phone number verification exercise was conducted to assess the magnitude of this problem. For all surveyed members, an up-to-date primary phone number was recorded for each individual. This exercise showed that only 48% of numbers in the data base matched the primary phone number stated by the member. Using this sample of recently verified phone numbers allows us to recruit a group of trial participants with a high likelihood of an SMS message reaching the intended recipient instead of another person (who may be in a different arm of the trial). This will allow for an evaluation with a high internal validity and result in an accurate treatment effect. However, this type of phone number verification exercise is very resource-intensive and may not be scalable to the entire population. Furthermore, the verified number sample was not representative of the member population in Kumasi, as older and female members were more likely to be found in the survey locations during the verification exercise. Therefore, we also draw a random, representative sample from the NHIS data base to test the same intervention at a larger scale in a more realistic setting (excluding all those with phone numbers which were recorded in verified group). This will allow for an evaluation with a high external validity and an intent-to-treat effect. It will also allow us to assess the value of additional information and the necessity of such verification exercises. By combining the two approaches, we are able to evaluate both the effectiveness of the intervention and the potential for scale-up, without having to sacrifice internal or external validity. In the verified number sample, the differently sized treatment arms result from the fact that insurance status and expiration dates are not distributed equally throughout the sample. As a result, Group 1 is the largest, followed by Group 2, while Group 3 is very small. For the unverified number sample, we are able to randomly select individuals from a much larger pool of members in the NHIS database. Here, we chose to randomly draw equally sized Groups 1–3, which will result in equally sized treatment arms.

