## Trial status

This is Protocol Version 2 from 08 November 2025 (following peer-review). Recruitment of trial participants began on 20 May 2024 (for the reminder intervention) and was completed on 19 September 2024. The interventions were completed as intended on December 31, 2024. Recruitment and surveying of participants for the follow-up survey and qualitative interviews was conducted in May 2025.

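### Group 1 members due within 90 days of launch may be depleted of early renewers, which confounds the treatment-intensity analysis and leaves the predicted underestimation unproven

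*Protocol article*

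**What the plan says.** Explanation for the choice of comparators {6b} forms the groups by expiry date. "Group 1 contains all individuals with active insurance and an expiration date during the intervention period", and "Group 3 contains all members with active insurance and an expiration date after the planned end date of our intervention period". Treatment is then randomised within each group.

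Background and rationale {6a} gives the renewal rules: "Members can renew their membership within 90 days before expiration", and "the NHIS relies on a system of annual re-enrolment of members".

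On timing, Eligibility criteria {10} states: "Participants must have active or recently expired NHIS membership at the starting date of the intervention". Recruitment {15} adds, for the unverified sample: "The remaining participants are recruited and enrolled automatically from the NHIS database right before the start of the intervention". Trial status reports a longer span: "Recruitment of trial participants began on 20 May 2024 (for the reminder intervention) and was completed on 19 September 2024".

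The statistical methods section {20a} compares each treated arm with its control over the whole of Group 1. The additional analyses section {20b} adds treatment-intensity variables to the logistic regression, to obtain an adjusted effect and the marginal value of one more message. The Discussion, under Explanation of design choice, expects the aggregate effect to be an underestimate because some members miss messages. Early and late expiry dates are treated there only as a matter of messages missed.

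**The concern.** Membership is annual, so a renewal should push the expiry date past a six-month period. A member due shortly after launch who had already renewed would then meet the Group 3 definition, and only those who had not renewed would remain in Group 1. A member due 90 days or more after launch could not have renewed yet. Group 1 would therefore join an early part that has lost its prompt renewers to a later part that is complete. Section {6b} uses the 90-day window to explain why Group 3 gets no reminders, but the article never applies it to Group 1.

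Three things are at stake:

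- **The control renewal rate.** Pooled over Group 1, it describes neither part.
- **The intensity analysis.** Members who miss the first reminder are those due within 28 days of launch, who are also the most depleted. Few messages and low renewal propensity go together.
- **The stated direction of bias.** Missed messages pull the aggregate effect down, but depletion can push it up, and the article names only the first.

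**Working it through.** The plan gives no figure on this point, so there is none to reproduce. The following is an illustration.

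**Inputs from the article.** The renewal window is 90 days ({6a}). The intervention lasts six months (Abstract), taken as 184 days; 20 May to 31 December 2024 (Trial status) is 225 days. On-time renewal E is 50%, since about half of insurance periods are renewed late or never ({6a}); 60% is the alternative, from the 40% with coverage gaps (Abstract). Any renewal is 81%, since 19% never renew (Abstract).

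**Assumptions.** Renewal updates the recorded expiry date, grouping is done once at launch, and expiries are evenly spread. F(u) is the share of on-time renewals made in the first fraction u of the window.

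**Depletion.** For expiry d days after launch (d < 90), the used fraction of the window is u = (90 − d)/90 and the missing share is s(d) = E × F(u). For d of 90 or more, s = 0. With average missing share S, the on-time rate among those left is (E − S)/(1 − S).

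**Even timing, F(u) = u, E = 0.50, 184 days:**

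- First 90 days: S = 0.50 × 0.50 = 0.25. On-time rate (0.50 − 0.25)/0.75 = 33%.
- All Group 1: S = 0.25 × 90/184 = 0.122. On-time rate (0.50 − 0.122)/0.878 = 43%. Any renewal (0.81 − 0.122)/0.878 = 78%, against 81%.

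**Other timings.** The later columns cover E = 0.50 and 0.60, giving the value at 0.50 first. The Group 1 columns are for 184 days.

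| Timing of on-time renewals | Mean of F | Missing, first 90 days | Missing, Group 1 | On time, first 90 days | On time, Group 1 |
|---|---|---|---|---|---|
| Front-loaded, 1 − (1 − u)² | 2/3 | 33%, 40% | 16%, 20% | 25%, 33% | 40%, 50% |
| Even, u | 1/2 | 25%, 30% | 12%, 15% | 33%, 43% | 43%, 53% |
| Late, u² | 1/3 | 17%, 20% | 8%, 10% | 40%, 50% | 46%, 56% |
| Very late, u⁴ | 1/5 | 10%, 12% | 5%, 6% | 44%, 55% | 47%, 58% |

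Over 225 days the even to very late rows give 4% to 12% missing from Group 1. Leaving out the front-loaded row, the range is therefore 4% to 15%. If almost everyone renews just before expiry, it is close to nil.

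**Intensity comparison with an intervention that does nothing** (even timing, E = 0.50, 184 days):

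- Due within 28 days, so missing the first reminder: mean u = (90 − 14)/90 = 0.844, S = 0.422. On-time rate (0.50 − 0.422)/0.578 = 13%.
- Due at 28 days or later: S = 0.50 × (62²/2)/90/156 = 0.068. On-time rate (0.50 − 0.068)/0.932 = 46%.

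A gap of 13% against 46% appears with no treatment effect. Over the even to very late timings and both values of E, the first figure runs from 13% to 41%.

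**Effect.** Suppose, for illustration, that treatment converts 10% of those who would not renew on time, and that the missing members could not have benefited.

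- Full cohort: 50% to 55%, 5.0 points, odds ratio (0.55/0.45)/(0.50/0.50) = 1.22.
- Group 1: 5.0/0.878 = 5.7 points, 43.0% to 48.7%, odds ratio 1.26 (1.23 to 1.28 over the four timings).
- First 90 days: 5.0/0.75 = 6.7 points, 33.3% to 40.0%, odds ratio 1.33 (1.25 to 1.44).

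**Net direction.** On the difference scale, depletion multiplies the effect by 1/(1 − S) = 1/0.878 = 1.14. Missed messages would have to remove more than S = 12% of the average effect before the aggregate fell below the full-cohort value. The article gives nothing from which to judge that.

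**The case against.** **The planned contrasts are sound.** Randomisation takes place within Group 1, after any depletion, and the primary metric is an odds ratio between arms. A reader might infer that the 1R and 1A results are biased, or that Group 1 is no real population. Neither follows: members unrenewed at launch are a real population, and reminders go only to members who have not renewed. This stands in full.

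**The mechanism is not stated.** The article does not say whether renewal overwrites the expiry date used for grouping. Section {18a} says the data hold the beginning and end of insurance periods, so grouping could rest on the current period. Early renewers would then sit in Group 1 as successes achieved before randomisation, and the directions above would reverse. A single launch-day grouping is also an inference from {10} and {15}, and Trial status must be reconciled with it. This stands, and is why the point is conditional.

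**External validity.** A reader might take "This will allow for an evaluation with a high external validity and an intent-to-treat effect" as a claim about all members due to renew. In context it contrasts a random database draw with the verified sample, which is unrepresentative by age and sex. Depletion does not refute that claim.

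**Partly handled.** Section {6b} expects members with imminent renewal dates to respond differently, and {20b} plans analyses by treatment received. These do not mention depletion, and the intensity variables are themselves confounded by it.

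**The later stratum is no clean substitute.** Arm 1R messages run from t−28 to t+89, so in 184 days only expiries on about days 28 to 95 receive all six. The stratum from day 90 has about 5 such days in 94 (46 in 135 for a 225-day period). It suits renewal by the expiration date, but not the other primary definitions. This stands and limits the fix.

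**Conclusion.** The point holds as a matter of interpretation and secondary analysis. If renewal updates the recorded expiry date, the part of Group 1 due within 90 days (90/184 = 49% of the expiry range, or 90/225 = 40%) is depleted of early renewers, and the article does not acknowledge it. Three consequences follow. The pooled control rate mixes two populations (43% instead of 50% on time in the even-timing case). Comparing outcomes across intensity levels confounds messages missed with renewal propensity. The flat prediction of an underestimate is not established.

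A reader might go further and say that the Group 1 effect is overstated by 4% to 17%, which is 1/(1 − S) for S from 4% to 15%. The documents do not support that as a finding. It needs assumed lead times, the overwrite assumption and an undiminished effect in members who miss messages. Even then the illustrative odds ratio moves only from 1.22 to 1.26. Size and net direction remain open.

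**What to change.** 1. State which expiry date was used for grouping, on what date, and how that fits the reported recruitment span. Describe Group 1 as members active and unrenewed at launch. If early renewers were in fact kept in Group 1, identify them by a renewal transaction dated before launch and say how they are handled.
2. Keep the all-Group-1 intention-to-treat estimate as primary.
3. Report 1R v 1C and 1A v 1C within strata fixed before randomisation: expiry under 90 days, and 90 or more days, from launch. Use the later stratum for the control rate and effect on renewal by the expiration date only, since it lacks most post-expiry messages.
4. Base the intensity analyses on arm contrasts within strata of expiry date, which fixes the scheduled messages in control members too, and not on outcomes compared across intensity levels.
5. In the Discussion, say that missed messages and depletion may act in opposite directions, and qualify the underestimation and scale-up statements accordingly.

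The cost is analysis and wording only, since expiry and renewal dates are already held. The grouping cannot change, because the interventions are complete. Stratum estimates are less precise: the later stratum covers 94 of 184 days (51%) or 135 of 225 days (60%) of expiries. If launch for an arm was as late as 19 September, 103 days before the end, it covers only 13 days and would carry little weight.
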